## Background

Diabetic kidney disease (DKD) is a leading cause of chronic kidney disease (CKD) in developed countries and is rapidly becoming the leading cause in developing countries as well [1]. It is one of the most common complications of diabetes mellitus affecting approximately 20–40% of diabetic patients in China; furthermore, it has replaced chronic glomerulonephritis as the leading cause of end-stage renal disease in middle-aged and elderly patients [2–4]. To address this, renin-angiotensin-aldosterone system (RAAS) inhibitors have recently been used; however, the prevalence of DKD remains unchanged [5, 6]. Therefore, exploring effective drugs for preventing DKD occurrence and development is critical.

Recently, increasing extensive clinical experience has supported the use of traditional Chinese medicine (TCM) for DKD. TCM with angiotensin receptor inhibitor treatment can reduce proteinuria in patients with type 2 diabetes [7]. Our previous retrospective study found that the Shenzhuo formula (SZF) improves glomerular filtration rate (GFR) and reduces 24-h urinary protein (24 h-UP) [8]. Another study of 88 patients with DKD found that the SZF improved estimated glomerular filtration rate (eGFR) and slowed DKD progression [8].

A previous study evaluated the 2-year effectiveness of SZF in the treatment of DKD and showed similar results with no significant changes in liver function and routine blood test results compared with the baseline; additionally, no patient experienced discomfort or severe adverse events [9].

However, comparisons between the effectiveness of SZF and RAAS inhibitors in patients with DKD remain lacking. Therefore, we designed and implemented a trial to investigate the effectiveness and safety of SZF and irbesartan in treating patients with DKD and macroalbuminuria. We hypothesized that SZF alone can improve macroalbuminuria secondary to DKD. Using SZF, we conducted a 24-week, randomized, multicentric, double-blinded, double-dummy, controlled clinical trial. The research protocol was previously reported [10]. The original protocol provides more details regarding the trial rationale, eligibility criteria, interventions, concomitant treatments, study visits, and data management.

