## Statistical principles

### Overall principles

After completion of the trial, all the statistical analysis tests will use two-sided tests with a nominal alpha level of 0.05, using the SAS [10, 12]. All confidence interval (CI) reports will be 95% CIs. For each outcome, the null hypothesis is the absence of difference between the intervention groups.

The description of measurement indicators will calculate the mean, standard deviation, median, minimum, maximum, and interquartile range (Q3–Q1). Normal continuous variables will be presented as the mean and standard deviation; non-normally distributed continuous variables will be presented as median with interquartile range. Counting indicators will be presented as the frequency and percentage of each category.

Inter-group comparisons will be performed with independent two-sample *t*-tests (normality, homogeneity of variance) or Wilcoxon rank-sum test (non-normality, heterogeneity of variance). Comparisons within normal and nonnormally distributed groups will be performed using paired *t*-test and paired rank-sum test, respectively. *χ*^2^ test or Fisher’s exact probability will be needed for count metrics, and the Wilcoxon rank-sum test will be used for categorical variables. A generalized linear mixed model analysis will be performed on the repeated measured outcome.

In situations where an imbalance in the baseline indicators exists, an adjustment will be required for the efficacy comparison of variables, such as age, sex, and concomitant treatment. The covariance method will be used for continuous variables, and logistic regression analysis was used for count metrics and hierarchical metrics.

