#### Secondary outcome analyses

The secondary outcome of the FAS and PPS will be analyzed, including serum creatinine (SCr, umol/L), eGFR (mL/(min×1.73 m^2^) using CKD-EPI creatinine equation [13]), urinary albumin excretion rate (μg/min), improvement in TCM symptoms, fasting blood glucose (mmol/L), 2-h postprandial plasma glucose (mmol/L), HbA1C (%), cholesterol (mmol/L), triglycerides (mmol/L), high density lipoproteins (mmol/L), low density lipoproteins (mmol/L), blood pressure (mmHg), albumin to creatinine ratio (ACR, mg/g), and the audit of diabetes-dependent quality of life 19 (ADDQoL) [14] The distribution and changes of all the secondary outcomes at the baseline and at each visit point will be compared between and within groups (Table 5).

**Table 5 Tab5:** Secondary outcome analysis

Time point	SZF, number, mean (SD)	Irbesartan, number, mean (SD)	Mean difference (95% CI)	***p*** Value
Scr at	*n* = xx	*n* = xx		
Week 0	xx (xx)	xx (xx)	xx (xx to xx)	.xx
Week 4	xx (xx)	xx (xx)	xx (xx to xx)	.xx
Week 8	xx (xx)	xx (xx)	xx (xx to xx)	.xx
Week 12	xx (xx)	xx (xx)	xx (xx to xx)	.xx
Week 16	xx (xx)	xx (xx)	xx (xx to xx)	.xx
Week 20	xx (xx)	xx (xx)	xx (xx to xx)	.xx
Week 24	xx (xx)	xx (xx)	xx (xx to xx)	.xx
Overall SZF effect ^a^				.xx
eGFR at	*n* = xx	*n* = xx		
Week 0	xx (xx)	xx (xx)	xx (xx to xx)	.xx
Week 4	xx (xx)	xx (xx)	xx (xx to xx)	.xx
Week 8	xx (xx)	xx (xx)	xx (xx to xx)	.xx
Week 12	xx (xx)	xx (xx)	xx (xx to xx)	.xx
Week 16	xx (xx)	xx (xx)	xx (xx to xx)	.xx
Week 20	xx (xx)	xx (xx)	xx (xx to xx)	.xx
Week 24	xx (xx)	xx (xx)	xx (xx to xx)	.xx
Overall SZF effect				.xx
UAER at	*n* = xx	*n* = xx		
Week 0	xx (xx)	xx (xx)	xx (xx to xx)	.xx
Week 4	xx (xx)	xx (xx)	xx (xx to xx)	.xx
Week 8	xx (xx)	xx (xx)	xx (xx to xx)	.xx
Week 12	xx (xx)	xx (xx)	xx (xx to xx)	.xx
Week 16	xx (xx)	xx (xx)	xx (xx to xx)	.xx
Week 20	xx (xx)	xx (xx)	xx (xx to xx)	.xx
Week 24	xx (xx)	xx (xx)	xx (xx to xx)	.xx
Overall SZF effect				.xx
FBG	*n* = xx	*n* = xx		
Week 0	xx (xx)	xx (xx)	xx (xx to xx)	.xx
Week 4	xx (xx)	xx (xx)	xx (xx to xx)	.xx
Week 8	xx (xx)	xx (xx)	xx (xx to xx)	.xx
Week 12	xx (xx)	xx (xx)	xx (xx to xx)	.xx
Week 16	xx (xx)	xx (xx)	xx (xx to xx)	.xx
Week 20	xx (xx)	xx (xx)	xx (xx to xx)	.xx
Week 24	xx (xx)	xx (xx)	xx (xx to xx)	.xx
Overall SZF effect				.xx
2hPG at	*n* = xx	*n* = xx		
Week 0	xx (xx)	xx (xx)	xx (xx to xx)	.xx
Week 4	xx (xx)	xx (xx)	xx (xx to xx)	.xx
Week 8	xx (xx)	xx (xx)	xx (xx to xx)	.xx
Week 12	xx (xx)	xx (xx)	xx (xx to xx)	.xx

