The improvement of TCM syndromes will be evaluated according to the symptom score method, which is conducted according to the nimodipine method [15]. Efficacy index = (score before treatment − score after treatment) /score before treatment × 100%. The criteria were as follows:

(a) *Clinical control* is defined as the resolution of most symptoms after treatment (efficacy index ≥ 95%); (b) *obvious therapeutic effect* is defined as marked improvement in most clinical symptoms (efficacy index ≥70%); (c) *with therapeutic effect* is defined as experiencing symptomatic relief (efficacy index ≥30%); (d) *invalid*: no significant improvement or symptom exacerbation (efficacy index < 30%).

Clinical efficiency will be calculated using the formula: Clinical efficiency = (clinical control case number + obvious therapeutic effect case number + with therapeutic effect number)/total number of cases × 100%.

The clinical efficiency of TCM syndrome scores after 24 weeks of treatment will be calculated for both groups (Table 6).

**Table 6 Tab6:** TCM syndrome score analysis

		SZF	SZF		Irbesartan	Irbesartan	
		Week 0	Week 24	***p*** Value	Week 0	Week 24	***p*** Value
		*n* = xx	*n* = xx		*n* = xx	*n* = xx	
Evaluation of TCM syndrome	Physical and mental fatigue	xx (xx)	xx (xx)	.xx	xx (xx)	xx (xx)	.xx
	Dry mouth and throat	xx (xx)	xx (xx)	.xx	xx (xx)	xx (xx)	.xx
	Weakness and soreness of the lower back and knees	xx (xx)	xx (xx)	.xx	xx (xx)	xx (xx)	.xx
	Qi deficiency and listlessness	xx (xx)	xx (xx)	.xx	xx (xx)	xx (xx)	.xx
	Spontaneous perspiration	xx (xx)	xx (xx)	.xx	xx (xx)	xx (xx)	.xx
	Night sweat	xx (xx)	xx (xx)	.xx	xx (xx)	xx (xx)	.xx
	Dysphoria in chest, palms, and soles	xx (xx)	xx (xx)	.xx	xx (xx)	xx (xx)	.xx
	Dark purplish lips	xx (xx)	xx (xx)	.xx	xx (xx)	xx (xx)	.xx
	Edema	xx (xx)	xx (xx)	.xx	xx (xx)	xx (xx)	.xx
Efficacy index	Clinical control	xx (xx%)	xx (xx%)	.xx	xx (xx%)	xx (xx%)	.xx
	Obvious therapeutic effect	xx (xx%)	xx (xx%)	.xx	xx (xx%)	xx (xx%)	.xx
	With therapeutic effect	xx (xx%)	xx (xx%)	.xx	xx (xx%)	xx (xx%)	.xx
	Invalid	xx (xx%)	xx (xx%)	.xx	xx (xx%)	xx (xx%)	.xx
	Overall clinical efficiency	xx (xx%)	xx (xx%)	.xx	xx (xx%)	xx (xx%)	.xx

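### Table 6 gives TCM-symptom results only within-arm p-values, contrary to the between-group comparison stated in the text, and assigns week-0 values to an efficacy index that has none

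*Protocol article*

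**What the plan says.** The Secondary outcome analyses section includes TCM symptoms in its list: "urinary albumin excretion rate (μg/min), improvement in TCM symptoms, fasting blood glucose (mmol/L"). It then says of the whole list that "The distribution and changes of all the secondary outcomes at the baseline and at each visit point will be compared between and within groups", and points to Table 5.

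The Overall principles section sets the hypothesis: "For each outcome, the null hypothesis is the absence of difference between the intervention groups". It names t and Wilcoxon rank-sum tests for comparisons between groups, and chi-square or Fisher tests for counts ("Fisher’s exact probability will be needed for count metrics, and the Wilcoxon rank-sum test will be used for categorical variables"). For change within a group it names paired tests ("Comparisons within normal and nonnormally distributed groups will be performed using paired" t or rank-sum tests).

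The text specific to TCM symptoms promises less. Symptom and total scores are to be described, and "The clinical efficiency of TCM syndrome scores after 24 weeks of treatment will be calculated for both groups (Table 6"). The efficacy index is the before-treatment score minus the after-treatment score, divided by the before-treatment score. Patients below 30% are classed as invalid; those at 30% or more count towards clinical efficiency.

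Table 6 has nine symptom rows and five efficacy-index rows (four categories and overall clinical efficiency). For each arm separately, every row has a week-0 cell, a week-24 cell and a p-value.

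**The concern.** There are two faults in the same table.

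First, its p-values address a null hypothesis other than the stated one. Change within an arm combines any drug effect with regression to the mean, background care and expectation. Only the comparison of the randomised arms isolates SZF against irbesartan, and Table 6 has no place for it. An analyst who fills in the table as printed would report no between-arm result for a named secondary outcome.

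Second, the efficacy index cannot be observed at week 0, because no after-treatment score exists then. The week-0 cells and the p-values beside them are either undefined or fixed by construction. Such p-values could be reported as significant improvement in either arm without saying anything about SZF relative to irbesartan.

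**Working it through.** The plan states no power or effect size for this outcome, so there is no figure to reproduce. The check has four steps.

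**1. Which comparisons the tables hold.**

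| Place | Between-arm comparison? |
|---|---|
| Overall principles | Yes: the null for each outcome is between groups |
| Secondary outcome analyses, general sentence | Yes: between and within groups, citing Table 5 |
| Table 4 (primary outcome) | Yes: difference, 95% CI, p-value |
| Table 5 (secondary outcomes) | Yes, but only 13 of the 14 listed outcomes have rows; TCM symptoms is the one missing |
| Table 9 (safety) | Yes: p-value between arms at each visit |
| Table 6 (TCM symptoms) | No |

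Table 6 has 9 + 5 = 14 rows and two p-value columns, so 14 × 2 = 28 p-values. All are within-arm, and 5 × 2 = 10 of them are on efficacy-index rows. It also has no row for the total score, although the text says that total scores will be described.

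**2. The index at week 0.** If the baseline score S stands in for the missing after-treatment score, the index is (S − S)/S × 100% = 0% for every patient with S > 0. All patients are then below 30%, so 100% are invalid and 0% respond, in both arms, before any treatment.

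**3. What the within-arm p-value then tests.** Assumptions: 60 analysed per arm (120 randomised 1:1, no losses), and the exact two-sided McNemar test. The test is my choice, because the article names none specifically for paired proportions. With no responders at week 0, every week-24 responder is a discordant pair in the same direction, so for r responders p = 2 × 0.5^r.

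- r = 5 (8.3%): p = 2 × 0.03125 = 0.0625
- r = 6 (10%): p = 2 × 0.015625 = 0.031

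Six responders are therefore enough for significance. The probability of at least 6 among 60 is a binomial tail. The true response rates are assumptions, because the article gives none:

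| True response rate | P(arm is significant) |
|---|---|
| 5% | 7.9% |
| 10% | 56.3% |
| 15% | 90.3% |
| 20% | 98.8% |

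If both arms truly respond at 20%, each is almost certain to show a significant improvement on the overall efficiency row, although the arms do not differ.

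**4. Whether the valid comparison is feasible.** Compare week-24 efficiency rates between 60 and 60 patients at two-sided 0.05, with power = Φ{[|p1 − p2|√60 − 1.96√(2p̄(1 − p̄))] / √(p1(1 − p1) + p2(1 − p2))}, where p̄ is the mean of p1 and p2. For 50% against 30% this is Φ{(1.549 − 1.358)/0.678} = Φ(0.28), or 61%. The same formula gives 59% for 60% against 40%, 82% for 75% against 50%, and 92% for 70% against 40%. These rates are again assumptions. The comparison can be made with tests that the article already names; it would detect large differences reliably and moderate ones less so.

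**The case against.** The strongest reply is that the plan does commit to a between-arm comparison. TCM symptoms is in the list of secondary outcomes, the general sentence covers all of them, the null is between groups for each outcome, and suitable tests are named. This stands. A reader might infer from Table 6 that TCM symptoms are tested only within arms; that is true of the table but not of the plan. The reply does not remove the mismatch. The general sentence points to Table 5, which has no TCM rows, and the TCM-specific text says only described and calculated. For the categories of 24-h urinary protein, by contrast, the article says expressly that they will be compared between groups.

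Three further inferences are not supported:

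- **The main hypothesis.** A reader might extend the fault to "We hypothesized that SZF alone can improve macroalbuminuria secondary to DKD". That statement concerns macroalbuminuria. The primary outcome, 24-h urinary protein, has a between-arm ANCOVA adjusted for baseline, and Table 4 carries a between-arm difference and CI. Table 6 has no bearing on it.
- **Non-inferiority.** A reader might add that no margin is given. The article refers its rationale and sample size to an earlier protocol that is not shown, and nowhere says that a non-significant result will be read as comparable efficacy.
- **A false-positive rate for significance in one arm only.** With equal true effects and power p per arm, that chance is 2p(1 − p), so it depends wholly on the assumed power. For the index rows at an assumed 20% response it is only 2 × 0.988 × 0.012 = 2.4%. The plan states neither such a power nor such a decision rule.

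It is also fair to say that within-arm tests of the raw scores are prespecified and can stand as description.

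**Conclusion.** The point holds as a defect of Table 6. The table contradicts the article's own null hypothesis and its general statement on secondary outcomes, and it assigns week-0 values and p-values to an index that does not exist at week 0. Both are errors in what the article prints, so condensation of a longer document does not explain them.

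Severity is modest. One secondary outcome is affected, and the primary analysis is not. For the index rows, all 10 p-values are uninformative about SZF versus irbesartan, and on the overall efficiency row 10% response is enough to reach significance within an arm. That threshold assumes 60 analysed per arm, baseline entered as the after-treatment score and an exact McNemar test. The conclusion that the week-0 index is undefined or fixed needs none of these assumptions.

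**What to change.** 1. Add to Table 6 a week-24 between-arm comparison with 95% CI and p-value for each symptom score and for the total score, which needs a row of its own. Adjust for the baseline score, or use the Wilcoxon rank-sum test already named if the scores are not normal. The scoring scale is not given in the article, so the choice between these should be stated.
2. For overall clinical efficiency, report the week-24 rate in each arm and the between-arm difference in proportions with 95% CI, tested by chi-square or Fisher.
3. Delete the week-0 cells and the within-arm p-values from all five efficacy-index rows.
4. Label within-arm changes in symptom scores as descriptive, and say in the text that conclusions on TCM symptoms rest on the between-arm estimate. Make the sentence that cites Table 5 cite Table 6 as well.

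The cost is a revised table shell and a few lines of text. No new data are needed, and with 100 of 120 patients reported as recruited, the change can precede the final analysis. The downside is that claims of improvement based on change within the SZF arm are given up.

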### Safety analyses

The safety analysis will analyze all patients in the safety set. The laboratory index will be listed individually in the following situations: the conversion of normal to abnormal laboratory findings and the occurrence of abnormal hepatic and renal function during the treatment; additionally, the association between conversion and medications will be analyzed. The type, severity, occurrence, and relationship between the intervention drug and all adverse events experienced during treatment will be tabulated (Table 7). The number and frequency of adverse events will be calculated for both groups. The occurrence of severe adverse events and subsequent drug discontinuation will be recorded in detail.

**Table 7 Tab7:** List of all adverse effects reported during the trial

Description	SZF, number	Irbesartan, number	Severity	Related to trial
xx	xx	xx	xx	xx
xx	xx	xx	xx	xx
xx	xx	xx	xx	xx

Any AE will be classified into three levels: mild, patients are able to tolerate discomfort without special treatment; moderate, patient will require special treatment to recover and tolerate the pain and discomfort; and severe, AEs that may lead to hospitalization, extended hospitalization, chronic severe disability, incapacity, or mortality. The relationship between AE and drugs will be assessed using standards from Measures for the Reporting and Monitoring of Adverse Drug Reactions, which was issued by the 2011 Ministry of Health of the People’s Republic of China.

The following relevance evaluations are listed in Table 8: (1) determining a possible relationship between the duration of drug use and suspicious adverse reactions; (2) the consistency of suspicious AE with other types of AE that are already known; (3) the explanations of the underlying mechanism of suspicious AE using pathological status, drug combination, and previous patient therapy; (4) the possibility of AE reduction or resolution after drug withdrawal or dosage reduction; and (5) the consistent occurrence of the same reaction after re-administration of the same drug. The incidence of adverse effects (AEs) will be compared between groups.

**Table 8 Tab8:** Relevance evaluation between AE and drugs

Judgment results	Judgment index				
	1	2	3	4	5
**Definite relevance**	+	+	−	+	+
**Probable relevance**	+	+	−	+	?
**Difficult to determine**	+	+	±	±	?
**Probable irrelevance**	+	−	±	±	?
**Definite irrelevance**	−	−	+	-	-

+ means affirmative, − means negative, ± means difficult to determine, ? means unclear situation. The incidence of ADR is calculated by using the sum of the cases of 1 + 2 + 3 as numerator, and the number of all cases as denominator

The safety assessment will include routine blood, urine, and stool tests; electrocardiogram; liver function tests, including alanine aminotransferase, aspartate aminotransferase, alkaline phosphatase, gamma-glutamyl transferase, and serum total bilirubin; and kidney function tests including blood urea nitrogen, SCr, uric acid, and β2-microglobulin levels at baseline, week 12, and week 24 (Table 9). Safety analysis will describe the distribution by qualitative judgment, which counts the number of cases and their proportion of abnormal indexes by cross-tabulation.

**Table 9 Tab9:** Safety assessment

		0 W			12 W			24 W		
		SZF	Irbesartan	***p*** value	SZF	Irbesartan	***p*** value	SZF	Irbesartan	***p*** value
		(***n*** = xx)	(***n*** = xx)		(***n*** = xx)	(***n*** = xx)		(***n*** = xx)	(***n*** = xx)	
**Hematology**	Red blood cell	xx (xx)	xx (xx)	.xx	xx (xx)	xx (xx)	.xx	xx (xx)	xx (xx)	.xx
	White blood cell	xx (xx)	xx (xx)	.xx	xx (xx)	xx (xx)	.xx	xx (xx)	xx (xx)	.xx
	Hemoglobin	xx (xx)	xx (xx)	.xx	xx (xx)	xx (xx)	.xx	xx (xx)	xx (xx)	.xx
	Platelet	xx (xx)	xx (xx)	.xx	xx (xx)	xx (xx)	.xx	xx (xx)	xx (xx)	.xx
**Urine test**	Glucose	xx (xx)	xx (xx)	.xx	xx (xx)	xx (xx)	.xx	xx (xx)	xx (xx)	.xx
	Ketone	xx (xx)	xx (xx)	.xx	xx (xx)	xx (xx)	.xx	xx (xx)	xx (xx)	.xx
	Occult blood	xx (xx)	xx (xx)	.xx	xx (xx)	xx (xx)	.xx	xx (xx)	xx (xx)	.xx
	Erythrocytes	xx (xx)	xx (xx)	.xx	xx (xx)	xx (xx)	.xx	xx (xx)	xx (xx)	.xx
	Leukocytes	xx (xx)	xx (xx)	.xx	xx (xx)	xx (xx)	.xx	xx (xx)	xx (xx)	.xx
**Stool routine**	Fecal leukocytes	xx (xx)	xx (xx)	.xx	xx (xx)	xx (xx)	.xx	xx (xx)	xx (xx)	.xx
	Feces occult blood	xx (xx)	xx (xx)	.xx	xx (xx)	xx (xx)	.xx	xx (xx)	xx (xx)	.xx
**Liver function**	ALT	xx (xx)	xx (xx)	.xx	xx (xx)	xx (xx)	.xx	xx (xx)	xx (xx)	.xx
	AST	xx (xx)	xx (xx)	.xx	xx (xx)	xx (xx)	.xx	xx (xx)	xx (xx)	.xx
	ALP	xx (xx)	xx (xx)	.xx	xx (xx)	xx (xx)	.xx	xx (xx)	xx (xx)	.xx
	GGT	xx (xx)	xx (xx)	.xx	xx (xx)	xx (xx)	.xx	xx (xx)	xx (xx)	.xx
	TBIL	xx (xx)	xx (xx)	.xx	xx (xx)	xx (xx)	.xx	xx (xx)	xx (xx)	.xx
**kidney function**	UA	xx (xx)	xx (xx)	.xx	xx (xx)	xx (xx)	.xx	xx (xx)	xx (xx)	.xx
	β2-microglobulin	xx (xx)	xx (xx)	.xx	xx (xx)	xx (xx)	.xx	xx (xx)	xx (xx)	.xx
	Serum albumin	xx (xx)	xx (xx)	.xx	xx (xx)	xx (xx)	.xx	xx (xx)	xx (xx)	.xx
	Blood urea nitrogen	xx (xx)	xx (xx)	.xx	xx (xx)	xx (xx)	.xx	xx (xx)	xx (xx)	.xx
**Electrocardiogram**		xx (xx%)	xx (xx%)	.xx	xx (xx%)	xx (xx%)	.xx	xx (xx%)	xx (xx%)	.xx
**Adverse events**	Mild	xx (xx%)	xx (xx%)	.xx	xx (xx%)	xx (xx%)	.xx	xx (xx%)	xx (xx%)	.xx
	Moderate	xx (xx%)	xx (xx%)	.xx	xx (xx%)	xx (xx%)	.xx	xx (xx%)	xx (xx%)	.xx
	Severe	xx (xx%)	xx (xx%)	.xx	xx (xx%)	xx (xx%)	.xx	xx (xx%)	xx (xx%)	.xx
	Overall AEs	xx (xx%)	xx (xx%)	.xx	xx (xx%)	xx (xx%)	.xx	xx (xx%)	xx (xx%)	.xx

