**Methods:**

This trial is a 24-week, randomized, multicentric, double-blinded, double-dummy clinical trial. A total of 120 patients with DKD will be equally and randomly divided into two groups: SZF+ irbesartan simulator or irbesartan + SZF simulator. The 24-h urinary protein change from baseline to week 24 is the primary outcome measure. The secondary outcome measures include serum creatinine, estimated glomerular filtration rate, urinary albumin excretion rate, improvement in traditional Chinese medicine symptoms, fasting blood glucose, 2-h postprandial plasma glucose, hemoglobin A1c, cholesterol, triglycerides, high density lipoprotein, low density lipoprotein, blood pressure, albumin to creatinine ratio, and the Audit of Diabetes-Dependent Quality of Life 19. Our recruitment began in May 2015; currently, we have recruited 100 participants, with a designed maximum sample size of 120. The interim results were reviewed at *N* = 60, and continuing recruitment was recommended. This statistical analysis plan includes our approach to missing data imputation, primary and secondary outcomes analyses, and safety endpoints.

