### Randomization and blinding

Eligible patients will be randomized in a 1:1 allocation ratio using a central permuted block randomization procedure (block size 4) with block sizes. The groups will include the TCM group, which will receive SZF and stimulated irbesartan, and the Western medicine group, which will receive SZF simulation agents and irbesartan capsules. Using the PROC PLAN process statement of SAS 9.4 (SAS/STAT Software 9.4, SAS Institute, Inc., Cary, NC, USA), a random arrangement (random coding table) of 120 subjects will be generated according to the number of seeds. The Institute of Basic Research in Clinical Medicine of the China Academy of Chinese Medical Sciences provides the random arrangement, 24-h emergency code break, and medical information. Participants, investigators, and statisticians will be blinded to treatment assignments.

SZF drugs and SZF simulators have identical shape, smell, and color, which were consistent when dissolved in water. Irbesartan capsules and simulators had consistent scent and appearance when the capsule was opened.

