## Status

The trial commenced in August 2014 and is scheduled to be completed in June 2022. Currently, 100 patients have been recruited.

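### Table 9 gives a p value but no between-arm difference or 95% CI for safety, and with at most 60 patients per arm non-significance cannot show comparable safety for adverse-event excesses up to about 10 points

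*Protocol article*

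**What the plan says.** The Background makes safety an aim: "we designed and implemented a trial to investigate the effectiveness and safety of SZF and irbesartan". Under Safety analyses the planned between-arm inference is "The incidence of adverse effects (AEs) will be compared between groups", with no effect measure, interval or margin named. Overall principles sets the test: "For each outcome, the null hypothesis is the absence of difference between the intervention groups", and "all the statistical analysis tests will use two-sided tests with a nominal alpha level of 0.05". Counts go to a chi-square or Fisher's exact test. The same section fixes 95% as the level of any confidence interval reported, but does not say which comparisons receive one.

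The table shells settle that:

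- **Table 9 (safety):** at weeks 0, 12 and 24, an SZF column, an irbesartan column and a p value. There is no difference and no interval.
- **Table 7 (AE list):** counts per arm, severity and relatedness, with no contrast.
- **Tables 4 and 5 (primary and most secondary outcomes):** a column for the mean difference with its 95% CI. Serum creatinine, eGFR and blood pressure are in Table 5 and so do get one.

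On size, the Abstract says "A total of 120 patients with DKD will be equally and randomly divided into two groups", the allocation is 1:1, and the Status section says "Currently, 100 patients have been recruited".

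**The concern.** A test of no difference answers whether the arms can be told apart. A safety claim needs the reverse: how large an excess of harm the data still allow. Only an interval shows that directly. In a trial with arms of this size, moderate differences in AE rate will usually be non-significant, so the p value column will be mostly unremarkable whether or not SZF carries some excess risk.

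At stake is the safety statement in the final report. If it rests on the p values in Table 9, it could describe SZF as comparable to irbesartan while an excess of 15 to 20 percentage points in an AE rate remains compatible with the same data. The Background shows how easily such wording arises: it reports an earlier SZF study as showing "no significant changes in liver function and routine blood test results compared with the baseline".

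**Working it through.** The article states no power, AE rate or margin for safety, so there is no figure of the plan's own to reproduce.

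**Inputs from the article**

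- Patients: 120, allocated 1:1, so n = 120/2 = 60 per arm at most. The safety set (treated at least once, with one safety assessment) cannot exceed this. At the 100 recruited so far, n is about 50.
- Test: two-sided, 0.05, chi-square or Fisher's exact.

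**Assumption:** AE rates. A range is shown.

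**Step 1. Miss rate.** For true rates p1 (irbesartan) and p2 (SZF), with X1 ~ Bin(n, p1) and X2 ~ Bin(n, p2):

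miss rate = 1 - sum over all (i, j) of P(X1 = i) x P(X2 = j) x 1[test p value <= 0.05].

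| Irbesartan v SZF | Fisher, n = 60 | Chi-square, n = 60 | Fisher, n = 50 |
|---|---|---|---|
| 5% v 10% | 91% | 83% | 94% |
| 5% v 15% | 67% | 54% | 76% |
| 10% v 20% | 75% | 67% | 81% |
| 20% v 30% | 82% | 75% | 85% |
| 20% v 40% | 40% | 32% | 49% |
| 10% v 30% | 27% | 20% | 36% |

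For excesses of 5 to 10 points, both tests miss more often than they detect. For excesses of 20 points, detection is the likelier result at n = 60.

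**Step 2. What the missing interval would show.** Take 10/60 on SZF and 5/60 on irbesartan, as illustrative counts.

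- Fisher p = 0.27.
- Risk difference = 10/60 - 5/60 = 16.7% - 8.3% = +8.3 points.
- Wilson 95% limits: SZF 9.3% to 28.0%; irbesartan 3.6% to 18.1%.
- Newcombe lower limit = 8.3 - sqrt((16.7 - 9.3)^2 + (18.1 - 8.3)^2) = about -4 points.
- Newcombe upper limit = 8.3 + sqrt((28.0 - 16.7)^2 + (8.3 - 3.6)^2) = about +21 points.

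The shell would print the two percentages and .27. The upper limit of 21 points would not appear.

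**Step 3. Other illustrative counts, n = 60 per arm, same method**

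| SZF v irbesartan | Fisher p | Difference (95% CI), points |
|---|---|---|
| 6 v 3 | 0.49 | +5.0 (-5.2 to +15.7) |
| 12 v 6 | 0.20 | +10.0 (-3.0 to +22.9) |
| 3 v 3 | 1.00 | 0 (-9.3 to +9.3) |
| 0 v 0 | 1.00 | 0 (-6.0 to +6.0) |

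All are non-significant, yet the excess risk left open ranges from 6 to 23 points.

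**Step 4. Continuous laboratory values.** The smallest difference with 80% power is (1.96 + 0.84) x sqrt(2/60) = 0.51 SD. Power for a 0.5-SD shift is 78% at 60 per arm. The power problem is therefore mainly one of AE rates, not of sizeable shifts in laboratory means.

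**The case against.** Several stronger readings are tempting, and the article does not support them.

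- **That safety is reported by p values alone.** It is not. Table 9 shows summaries per arm, and the section also plans listings of normal-to-abnormal conversions, cross-tabulated proportions abnormal, an ADR incidence, and AE type, severity and relatedness by arm. A reader could work out a risk difference and interval from the counts. That stands, but the plan should print the quantity that its safety conclusion needs.
- **That intervals were left out selectively for safety.** Serum creatinine, which is named as a kidney safety test, gets a difference and 95% CI in Table 5, as do eGFR and blood pressure. Table 6, an efficacy table, also lacks them. No selective choice can be inferred.
- **That the plan will treat non-significance as safety.** No section says so. The Background sentence describes an earlier study's comparison with its own baseline and is not a decision rule here. The misreading is a foreseeable risk, not a stated rule.
- **That the tests would miss most harms that matter, even a doubling or tripling of an AE rate.** The figures do not bear this out in general. Rises from 20% to 40% and from 10% to 30%, and a 0.5-SD laboratory shift, would more often be detected than missed at 60 per arm.
- **That Table 9 will yield a predictable number of chance findings, taken as 5% of its p values.** Fisher's test at low counts rejects well below 5%, and the AE rows overlap (three grades plus the total), so that count would be too high.

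It can also be said that low power for AEs is inherent at this size and that an interval displays it without curing it. That is true, and displaying it is the purpose. Lastly, an article may leave detail to a fuller plan. Here, however, the shell itself is printed and fixes the output columns.

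**Conclusion.** The point holds in limited form. Table 9 fixes the between-arm safety contrast as summaries per arm plus a p value, without the difference and 95% CI that Tables 4 and 5 carry. With at most 60 per arm, Fisher's test misses 67% to 91% of the assumed AE excesses of 5 to 10 points, and the chi-square test 54% to 83%. A non-significant p value therefore cannot support comparable safety for excesses up to about 10 points. For larger excesses the case weakens: the Fisher miss rate is 40% for 20% v 40% and 27% for 10% v 30%.

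These sizes rest on assumed AE rates, because the article gives none, and on full recruitment with every patient in the safety set. Fewer patients make them worse. The absence of the difference and interval columns rests on no assumption. This should be changed before the final analysis. It concerns reporting and interpretation and does not invalidate the safety data.

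**What to change.** In Table 9 and the AE summary, add the SZF-minus-irbesartan contrast with its 95% CI:

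- a risk difference with a Newcombe or exact interval for AEs by grade and overall, ADRs, the ECG and proportions abnormal;
- a mean difference for continuous laboratory values, as Table 5 already does.

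Add to Safety analyses a sentence such as: *The safety conclusion will be based on the estimated differences and their 95% confidence intervals, including the upper limit of the excess risk with SZF; a non-significant difference will not be taken as evidence of comparable safety.* The p values may stay.

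The cost is wording and table shells; no new data are needed. The downside is that the intervals will be wide, so the safety statement will look less favourable than a column of non-significant p values.
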